### Statistical Analysis

#### Analysis Plan

The protocol will favor an intention-to-treat approach for the analysis of results. Data analysis will be performed in SPSS (IBM Corp). Baseline demographic information will be summarized using descriptive statistics. Continuous variables will be summarized with means and SDs. Categorical variables will be summarized with counts, proportions, and medians (IQR). The distribution of continuous variables will be assessed using graphical inspection and the Shapiro-Wilk test for normality. If the assumption of normality is not met, equivalent nonparametric approaches or data transformation will be used. The multiple testing problem will be accounted for using Bonferroni correction. All hypothesis tests will be 2-sided, and the familywise Type I error rate will be controlled at α=.05 using Bonferroni-adjusted significance thresholds. If needed, statistical analysis will also be conducted after controlling for baseline demographics and clinical characteristics (eg, age, sex, and race).

The effects of treatment on continuous variables will be evaluated using linear mixed models with fixed effects consisting of a time factor (before to after the experimental session; before treatment to 3-month follow-up) and a between-participants treatment factor (MB vs MB+DP vs WLC, as appropriate). If necessary, we will adjust for randomization imbalance by co-varying baseline variables. Little’s Missing Completely at Random (MCAR) test will be used to determine if data are missing completely at random. We will use maximum likelihood estimation procedures to deal with missing data according to an intent-to-treat philosophy that is robust against common patterns of missing data. The maximum likelihood estimation is based on all data observations; no values are deleted or imputed.

All EEG analyses will be performed in MATLAB (Matrix Laboratory; MathWorks) using scripts implementing the EEGLAB toolbox [48]. First, epochs of 300 s will be created for each participant. Then, the signal will be notch-filtered at 60 Hz and low-pass filtered at 40 Hz cutoff using a fourth-order Butterworth filter and high-pass filtered at 0.1 Hz cutoff using a second-order Butterworth filter. Filtered data will be passed through the PREP pipeline [49] which detrends the data, applies a notch filter tapering off the harmonics of 60 Hz, rereferences the data to the linked earlobe, and identifies and interpolates bad channels. Interpolation in low-density montages has been shown to produce valid data [49,50]. In the power spectral density analyses, average power spectra in the theta (4-8 Hz) band will be calculated using Welch periodogram across frontal midline sites.

All fNIRS data will be preprocessed in MATLAB as follows: detected NIR light will be transformed into O₂Hb and HHb concentrations using the modified Beer–Lambert law. Motion artifacts will be corrected using temporal derivative distribution repair, followed by band-pass filtering (0.01-0.1 Hz). Low-amplitude motion artifacts will be corrected using the algorithm of Cui et al [51], and single artifact-laden channels will be interpolated. A Gaussian PCA kernel will be applied to remove global signal components. Finally, signals will be converted to *z* scores to facilitate comparisons across participants.

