### Participants

We will recruit and enroll 173 adults with CMP who meet established eligibility criteria. Sample size estimation was conducted in 2 stages, reflecting an expansion from a sole focus on mechanistic sensitivity to the joint consideration of mechanistic and clinical relevance. The first stage was designed to detect changes in self-transcendence in order to elucidate an emerging therapeutic mechanism of MBIs, whereas the second stage broadened the scope of the study to contribute to a growing body of research evaluating the effects of brief MBIs on chronic pain.

First, our original power analysis using G*Power (Heinrich Heine University Düsseldorf) indicated that a total sample of 138 participants would provide sufficient power (*β*=.80) to detect changes in self-reported and psychophysiological indices of self-transcendence [42]. This target reflected a required analyzable sample of 110, inflated by 25% to account for expected attrition. To promote robust detection of mechanistic effects, we specified a conservative effect size ( Cohen *d*=0.30), representing half the smallest effect observed in our preliminary data (Cohen *d*=0.60). This approach was intended to support the more stringent comparison between the MB and MB+DP groups, while incorporating corrections for multiple comparisons.

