Second, to enhance the clinical interpretability of the intervention effects, we added a waitlist control group. This adjustment was made prior to participant enrollment. Inclusion of this no-treatment comparison group provides a benchmark against which to evaluate the specific impact of the MBIs on both mechanistic and clinical outcomes, relative to the natural progression of symptoms in the absence of additional intervention. This control arm was designed to be half the size of each active treatment group (n=35), resulting in a total sample size of 173 and preserving a 2:2:1 randomization ratio. This total sample size (n=173) is consistent with a G*Power estimate for a 3 (group)×2 (time) mixed design, assuming a small effect (Cohen *d*=0.30), 80% power, and a Bonferroni-adjusted alpha of .0125 for 4 pairwise comparisons (ie, self-reported self-transcendence; 2 psychophysiological indices of self-transcendence, including frontal midline theta activity and DMN activity, and acute pain). Beyond these primary group-level effects, the planned sample size also supports Aims 2 and 3. Specifically, a G*Power analysis (2-tailed, *α*=.0167, corrected for multiple comparisons; power=0.80) indicated that 112 participants are sufficient to detect a moderate association (*r*=0.30) among phenomenological and psychophysiological indices of self-transcendence, well below the planned sample of n=173. Finally, this sample size is adequate for the planned mediation analyses; the parallel multiple-mediator model for acute pain includes 19 estimated parameters, yielding approximately 9.1 observations per parameter with n=173, consistent with the commonly cited 5‐10 observations per parameter convention.

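### Bonferroni is valid and matches the sizing alphas, but Holm's step-down controls the same familywise .05 and never rejects less; the gain depends on how many effects are real

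*Protocol article*

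**What the plan says.** The Analysis Plan section fixes the method: "The multiple testing problem will be accounted for using Bonferroni correction". It adds "All hypothesis tests will be 2-sided" and that the "familywise Type I error rate will be controlled at α=.05 using Bonferroni-adjusted significance thresholds". It does not mention simultaneous confidence intervals; the correction is used only to set significance thresholds.

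The Participants section uses the same correction for sample size. The three-arm calculation assumes "a Bonferroni-adjusted alpha of .0125 for 4 pairwise comparisons". The four items listed there are self-reported self-transcendence, frontal midline theta, DMN activity and acute pain. The calculation is described as "assuming a small effect (Cohen *d*=0.30), 80% power". The Aim 2 correlations are sized at .0167, giving 112 participants for r = 0.30.

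**The concern.** Single-step Bonferroni tests each member of a family of m hypotheses at .05/m, whatever the other results show. Holm orders the p-values and tests the smallest at .05/m, the next at .05/(m-1), and so on, stopping at the first failure. Its familywise guarantee is the same and needs no assumption about how the tests are correlated. Because every Holm threshold is at least as large as Bonferroni's, Holm can only add rejections.

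The difference matters most when several effects in a family are real, and that is what this trial predicts. The Aim 1 and Aim 3 hypotheses expect movement in NADA-S, theta, the DMN proxy and acute pain. The Discussion says that agreement between self-report and the physiological indices would strengthen the inference about mechanism. A rule that holds the later tests at the strictest threshold makes such agreement harder to show.

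**Working it through.** **Plan's own figures.** Family of four: .05/4 = .0125, as stated. Family of three: .05/3 = .0167, as stated. Aim 2 sample size by Fisher's z: ((z(1 - .0167/2) + z(.80)) / atanh(0.30))² + 3 = ((2.394 + 0.842)/0.3095)² + 3, which is about 112.2 and agrees with the stated 112. The analysis rule and the sizing rule therefore use the same correction.

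**Thresholds for four tests.** Bonferroni: .0125 for all. Holm: .0125, .0167, .025, .05 in order of p-value.

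**Simulation.** Inputs from the plan are four tests, two-sided, familywise .05, and 80% power at .0125. The mean of each real effect's test statistic is z(.99375) + z(.80) = 2.498 + 0.842 = 3.339. The correlation between test statistics is not given in the article; I assumed 0, 0.3 and 0.5. There were 200,000 replicates per setting. Ranges run over the three correlations.

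| Real effects (of 4) | Average power, Bonferroni | Average power, Holm | All real effects detected, Bonferroni | All real effects detected, Holm |
|---|---|---|---|---|
| 1 | 80% | 80.1% | 80% | 80.1% |
| 2 | 80% | 81.9-82.3% | 64-69% | 69-72% |
| 3 | 80% | 84.3-85.3% | 51-61% | 64-71% |
| 4 | 80% | 87.5-89.5% | 41-56% | 69-76% |

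As a hand check, four independent tests at 80% power are all positive under Bonferroni with probability 0.80⁴ = 0.41, the lower end of the range in the last row.

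**First rejection.** The chance of at least one rejection is identical under both rules in every setting, because both test the smallest p-value at .0125.

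**Realised familywise error (Bonferroni against Holm).**
- All four nulls true: 4.4-4.9% under both.
- Three true nulls: 3.4-3.7% against 4.2-4.6%.
- Two true nulls: 2.3-2.5% against 3.8-4.4%.
- One true null: 1.2-1.3% against 3.7-4.0%.

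Holm stays below 5% throughout.

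**Sensitivity to the 80%.** If each of four real effects had only 50% power at .0125, average power would rise from 50% to about 59%, and the chance of detecting all four from 6-20% to 22-39%.

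**Aim 2 family.** With three real correlations, each at 80% power at .0167, the chance of detecting all three rises from 51-61% to 72-77%.

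**The case against.** The strongest reply is that nothing here is wrong. Bonferroni is prespecified, valid under any dependence and matched to the alphas behind the sample size, so its cost is already in the planned N. That stands, and the point is one of efficiency only.

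Several stronger readings are tempting, and the document does not support them:

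- A reader might infer that real effects are being missed for nothing. The stated 80% power is already claimed at the Bonferroni threshold, and Holm adds nothing until a first hypothesis is rejected. It also gains its power by using error that Bonferroni leaves unspent: with two true nulls, realised familywise error rises from about 2.4% to about 4%. That is within the stated .05, but it is not free.
- A reader might infer that correlated outcomes favour Holm. They do not. With four real effects, the average gain falls from 9.5 points at correlation 0 to 7.4 at 0.5. What matters is how many effects are real.
- A reader might infer that the trial succeeds only if all indices are positive. No such criterion is stated. Aim 1 names NADA-S as the primary outcome, and the Discussion treats divergence between mechanism and pain results as informative too.

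Two practical objections carry some weight. Holm lacks the simple simultaneous intervals that Bonferroni gives, although the Analysis Plan section does not call for them. Recruitment began on October 28, 2024, so this would be a change to a less strict rule during the trial. A dated amendment before any outcome is analysed by arm answers that, since the stated .05 is kept.

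**Conclusion.** The point holds as a cheap improvement to a valid plan. At the trial's own familywise .05, Holm is never less powerful than the stated rule. The benefit ranges from negligible with one real effect (0.1 points of average power), through about 2 points with two and 4-5 with three, to 7-10 points with four. If all four effects are real, the chance of showing all of them rises by roughly 20 to 28 points.

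These figures assume that the stated 80% power at .0125 applies to each test, approximately normal test statistics, and equal correlations of 0 to 0.5 that the article does not give. The ordering of the two rules needs none of these assumptions.

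Holm does not settle what belongs to a family. The Participants section calls four outcomes pairwise comparisons, while three arms allow up to three contrasts per outcome. The families must be named under either rule.

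**What to change.** In the Analysis Plan section, replace both mentions of Bonferroni with wording such as: multiplicity will be handled by Holm's step-down procedure at a two-sided familywise .05 within each named family. Name the families, for example (a) the four outcomes listed in the Participants section, stating which group test or contrast each one uses, and (b) the three Aim 2 correlations.

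Keep .0125 and .0167 in the Participants section, described as conservative sizing alphas. They are Holm's first-step thresholds, so no sample-size figure changes.

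Report Holm-adjusted p-values. Any unadjusted 95% intervals shown beside them must be labelled as unadjusted and not used for significance claims, because such an interval can exclude zero where the Holm test does not reject.

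Issue the change as a dated, versioned amendment before any outcome is analysed by arm, and communicate it to the registry as the Results section provides for substantial amendments. The cost is a few sentences and the loss of simple simultaneous intervals; no participants or data are added.

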### Assignment of Interventions and Blinding

Participants will be randomly assigned to intervention groups using a computer-generated randomization sequence created in Microsoft Excel. Randomization is stratified by opioid use (yes or no) to ensure balance across treatment arms on this clinically relevant variable. Within each stratum, participants are allocated using permuted block randomization with a fixed block size of 6 to maintain allocation concealment and prevent prediction of assignment. Treatment allocation is generated by personnel uninvolved in assessment or treatment and concealed on the private, password-protected computer of the uninvolved research member.

To preserve blinding, the randomization sequence will not be accessible to either assessment staff or the principal investigator (PI) until the study’s completion. Treatment allocation, for active treatment groups, will only be revealed to the interventionist immediately before the participant’s first treatment appointment. Outcome assessor blinding will further be ensured through the use of online, asynchronous self-report surveys, preventing any direct interaction between study personnel and participants.

Unblinding will only occur in exceptional circumstances where knowledge of the assigned intervention is essential for the clinical safety of the participant or to address a serious adverse event (AE). The request for unblinding must be made by the PI or a designated senior clinical investigator after determining that unblinding is necessary for participant safety or ethical oversight. The PI will document the rationale for unblinding and notify the institutional review board (IRB) if the event involves a serious adverse reaction or protocol deviation that may impact participant safety or data integrity.

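### The treatment-effect model omits the opioid-use stratum and adjusts for baseline only if imbalance is seen, which leaves the primary model open and gives up precision that baseline adjustment would supply

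*Protocol article*

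**What the plan says.** In the protocol article, Assignment of Interventions and Blinding states: "Randomization is stratified by opioid use (yes or no) to ensure balance across treatment arms on this clinically relevant variable".

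The Analysis Plan then describes the models for continuous outcomes as "linear mixed models with fixed effects consisting of a time factor", together with a between-participants treatment factor for the three arms. Opioid use is not listed, and neither is the outcome's baseline value as a covariate.

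Covariates appear in two conditional sentences:

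- On imbalance: "If necessary, we will adjust for randomization imbalance by co-varying baseline variables".
- On patient characteristics: "If needed, statistical analysis will also be conducted after controlling for baseline demographics and clinical characteristics", with age, sex and race as the examples.

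Neither sentence gives a criterion or a fixed list, and neither names opioid use. The only covariates fixed in advance are in Aim 3, where the mediation models adjust for pain before the session and for the mediators' baseline values. No section puts the opioid stratum or the baseline outcome into the treatment-effect models for Aim 1 or for the clinical outcomes.

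**The concern.** There are three parts, of unequal weight.

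1. **The covariate rule.** Under valid randomisation any baseline imbalance is due to chance. Its size does not show whether the variable predicts the outcome, and that is what makes adjustment worthwhile. With no criterion and no variable list, the primary model is settled only after the data have been seen.
2. **The use of baseline.** If the pre-treatment value enters only as one level of the time factor, with arm means free to differ there, the time-by-treatment contrast has the precision of a change score. Using the same value as a covariate gives a smaller standard error at no cost in recruitment. This matters most for MB+DP against MB, which the Participants section calls the more stringent comparison.
3. **The stratum.** Stratified allocation balances the arms on opioid use. If the stratum predicts the analysed quantity but is left out of the model, the reported standard error is larger than the true one.

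**Working it through.** **Inputs from the document.** Total 173, allocated 2:2:1, so 173 × 2/5 ≈ 69 in each active arm and about 35 on the waitlist; two-sided tests; Bonferroni-adjusted alpha 0.0125; one binary stratum.

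**Inputs the document does not give.** The pre-post correlation ρ, and the strength of the link between opioid use and any outcome. Both are shown below as assumed ranges.

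**The plan's own figure.** The article gives no precision figure for adjustment. Its total of 173 is the sum 138 + 35. The accompanying power statement for a 3 × 2 mixed design cannot settle ρ, because ρ is not stated. With f = d/2 = 0.15, alpha 0.0125 and 80% power, the within-between interaction needs 212 participants at ρ = 0.3 and 153 at ρ = 0.5.

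**Baseline as a time level or as a covariate.** Take one pre- and one post-measurement with equal variance σ².

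- Variance of change: 2σ²(1 − ρ).
- Residual variance with baseline as covariate: σ²(1 − ρ²).
- Variance ratio: 2(1 − ρ)/(1 − ρ²) = 2/(1 + ρ). The standard-error ratio is its square root.

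| ρ (assumed) | Variance ratio | SE ratio | SE wider by |
|---|---|---|---|
| 0.3 | 2/1.3 = 1.54 | 1.240 | 24% |
| 0.5 | 2/1.5 = 1.33 | 1.155 | 15.5% |
| 0.7 | 2/1.7 = 1.18 | 1.085 | 8.5% |

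**Omitting the stratum.** Reported SE divided by true SE = 1/√(1 − R²), where R² is the share of variance in the *analysed* quantity that the stratum explains. For a change contrast, that quantity is the change. A stratum effect that is constant over time cancels and contributes nothing.

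A simulation of MB against MB+DP shows both cases. It used N = 173, 6,000 runs per scenario, and assumed values of 30% opioid users, ρ = 0.5, residual SD 1 and a 0.5 SD stratum effect on level. It used blocks of 5, because the article's "participants are allocated using permuted block randomization with a fixed block size of 6" cannot hold a 2:2:1 ratio; that is a separate matter to reconcile.

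| Stratum effect on change | Change, no stratum | Change + stratum | Baseline + stratum |
|---|---|---|---|
| None | 0.1697 | 0.1697 | 0.1474 |
| 0.5 SD | 0.1742 | 0.1697 | 0.1475 |

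(Entries are mean standard errors.)

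- With no effect on change, adding the stratum to the change model alters nothing.
- With a 0.5 SD effect on change, omission widens the SE by 0.1742/0.1697 − 1 = 2.7%. The formula agrees: the stratum variance is 0.5² × 0.3 × 0.7 = 0.0525, the residual variance of change is 2(1 − 0.5) = 1, so R² = 0.0525/1.0525 = 0.050 and 1/√0.95 = 1.026.
- At R² = 0.05, the actual type I error at nominal 0.0125 is 0.0104, and power of 80% becomes 78.1%. The test is conservative.
- Going from change + stratum to baseline + stratum gives 0.1697/0.1475 = 1.15, in line with the analytic 1.155.

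**The case against.** - **This is a condensed article.** Listing the stratum as a model term is often left to the full protocol or SAP, and the same sentence does not even name the time-by-treatment interaction that Aim 1 requires. Silence alone would indeed be no finding. But the article goes further: it lists the fixed effects and states an imbalance-triggered rule. That rule is a choice made in the text.
- **A reader might infer that omitting the stratum clearly widens the intervals, by several per cent.** The document does not support that. It gives no association between opioid use and NADA-S, theta, fNIRS connectivity or pain, and a time-constant effect cancels from a change contrast. For the same reason, adding only a stratum main effect to a repeated-measures model would change little.
- **A reader might infer that baseline data are ignored, or that a quarter to a third of the information is lost.** Baseline is used, as a time level under maximum likelihood. The loss is 1 − 1/1.54 = 35% at ρ = 0.3 and 1 − 1/1.33 = 25% at ρ = 0.5, but 1 − 1/1.18 = 15% at ρ = 0.7. The formula also assumes one pre- and one post-measurement. NADA-S and acute pain are taken before and after both Session 1 and Session 4, and the surveys at T0 to T3, so it does not transfer exactly.
- **A reader might infer that results will be picked from adjusted and unadjusted models.** In the simulation, taking the most favourable of four models gave type I error of 6.7–7.8% at nominal 5% and 1.9–2.1% at nominal 1.25%. That is a worst case. The stated trigger is baseline imbalance, not outcome results, and the demographic adjustment is worded as additional to the main analysis, which is close to a sensitivity analysis. What stands is that the text does not fix which model is primary.
- **The planned model matches the sizing.** The trial is sized for a 3 × 2 mixed design, so a repeated-measures model is consistent with it. Baseline adjustment is a better method; its absence is not an error of validity.

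**Conclusion.** The point holds as a low-cost improvement and as a rule that should be closed. Tying covariates to observed imbalance, without a criterion or named variables, leaves the primary model open.

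The precision gain forgone from baseline adjustment is an SE about 8.5% to 24% wider for assumed ρ from 0.7 down to 0.3. This rests on one pre- and one post-measurement with equal variances, and on reading the model as time-by-treatment with unconstrained baselines.

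The stratum is the weaker part. Its omission is conservative, matters only if opioid use predicts change or if post-treatment levels are analysed, and may cost little.

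**What to change.** Replace the two conditional sentences in the Analysis Plan with a fixed rule:

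- Every primary treatment model includes the outcome's pre-treatment value as a covariate: the pre-Session-1 value for NADA-S, acute pain, EEG and fNIRS, and the T0 value for survey outcomes.
- Every primary treatment model includes the opioid-use stratum. If a repeated-measures model with baseline as a time level is kept, it also includes stratum-by-time.
- Adjustment triggered by observed imbalance is deleted.
- Any model adjusted for age, sex or race is a named sensitivity analysis.

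Add one caveat. Table 4 places allocation before Week 1, so the pre-Session-1 measures are taken after assignment. In comparisons with the waitlist, adjusting for them assumes that knowing the assignment did not shift them. They should not be constrained equal across arms without stating that assumption. The T0 surveys precede allocation in Table 4, so they do not raise this issue.

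The cost is a short amendment and a few degrees of freedom. Recruitment is expected to run to May 2027, so the rule can be fixed before the final data are analysed.

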#### Primary Psychophysiological Outcomes

Frontal midline theta power will be measured by EEG. In Sessions 1 and 4, participants in the active treatment groups (MB and MB+DP) will complete psychophysiological data collection during a 5-minute resting baseline prior to treatment and throughout the 15-minute mindfulness practice. During the same sessions, participants in the WLC group will undergo a 5-minute resting baseline followed by a 15-minute time-matched control period. During all psychophysiological assessments, EEG will be continuously recorded from 10 midline scalp sites (Fz, F3, F4, FC1, FC2, FCz, Cz, CP1, CP2, and PZ) using an active sensor cap with Ag-AgCl electrodes (actiCap GmbH). In addition, vertical electrooculograms will be recorded. All recordings will be collected with an actiCHamp amplifier (Brain Products GmbH). Data will be acquired at a sampling rate of 500 Hz, a resolution of 0.489 µV and an amplification cutoff of 140 Hz, with impedances kept below 10 kilohms.

Connectivity in a validated fronto-temporal-parietal cortical proxy of DMN activity (ie, connectivity in-between channels belonging to the medial prefrontal cortex and the left and right MTG and STG, left and right posterior temporoparietal lobe, left and right temporoparietal junction will be measured by fNIRS during a 5-minute resting baseline period before treatment and during the 15-minute mindfulness practice. Hemodynamic responses to neuroactivation via oxy-, deoxy-, and total hemoglobin changes in the cerebral cortex will be measured with the NIRx NIRSport 2, a user-friendly, modular, and robust wireless fNIRS platform. The automated signal optimization algorithm ensures optimal signal quality before a measurement is started. Once data are being recorded, oxygenated hemoglobin and hemoglobin concentration changes can be visualized in real-time in several display modes. In addition, high-end whole-head visualizations are immediately available.

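### As written, the EEG pipeline computes frontal theta with no ocular-artifact step although vertical EOG is recorded, so blinks can be counted as theta

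*Protocol article*

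**What the plan says.** Under Primary Psychophysiological Outcomes, the protocol article describes the recording: "EEG will be continuously recorded from 10 midline scalp sites (Fz, F3, F4, FC1, FC2, FCz, Cz, CP1, CP2, and PZ"). It continues: "In addition, vertical electrooculograms will be recorded". The sampling rate is 500 Hz. The active arms are recorded at rest and through the guided practice, while "participants in the WLC group will undergo a 5-minute resting baseline followed by a 15-minute time-matched control period". The section does not say whether eyes are open or closed in any of these periods.

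Under Analysis Plan, the EEG steps come in order:

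- 300-second epochs and a 60 Hz notch;
- a low-pass step ("low-pass filtered at 40 Hz cutoff using a fourth-order Butterworth filter") and a high-pass step ("high-pass filtered at 0.1 Hz cutoff using a second-order Butterworth filter");
- PREP, whose functions are listed as detrending, line-harmonic removal, rereferencing, and detection and interpolation of bad channels;
- the outcome itself: "average power spectra in the theta (4-8 Hz) band will be calculated using Welch periodogram across frontal midline sites".

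The EOG is not mentioned again. For fNIRS, the same section does write out artifact handling: two motion-correction steps and interpolation of artifact-laden channels.

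**The concern.** Blinks are brief, large deflections that are strongest at the front of the head, and part of their energy lies in 4-8 Hz. The theta outcome is averaged over frontal midline sites, so it is exposed to them. The recipe is specific down to filter order, yet it contains no step that removes them and gives no use to the one channel recorded that could.

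Theta is listed with the primary outcomes in the abstract and under Measures, and as a secondary outcome in Aim 1. It also enters the Aim 2 correlations and is one of the Aim 3 mediators. The Discussion counts on agreement between self-report and independent physiological indices to strengthen the causal argument. If part of measured theta is eye activity, and eye activity follows the assigned task, that argument is weakened.

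**Working it through.** The plan gives no figure to reproduce here. The check has four steps.

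**1. Does any listed step remove blinks?** The notch acts at 60 Hz. Detrending and the 0.1 Hz high-pass act on slow drift. Rereferencing does not target eye activity. Interpolation replaces channels judged bad, whereas blinks are transient events on good channels. No segment rejection is listed. So no.

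**2. Do the filters attenuate 4-8 Hz?** The power gain of a low-pass Butterworth filter of order n and cutoff fc is 1/[1 + (f/fc)^(2n)]. At 8 Hz with fc = 40 and n = 4, (8/40)^8 = 2.56 × 10⁻⁶, so the gain is 1.000. For the high-pass at 4 Hz with cutoff 0.1 Hz and order 2, (0.1/4)^4 = 3.9 × 10⁻⁷, so the gain is again 1.000. Evaluating the digital filters at 500 Hz sampling gives the same at 4, 6 and 8 Hz. Blink energy in the theta band passes intact.

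**3. How much theta could blinks add?** All blink and background values here are assumptions. For Gaussian blinks of peak A, standard deviation σ = width at half height/2.355, and rate λ per second, the added one-sided spectrum is

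S(f) = 2λ · A² · 2πσ² · exp[−(2πfσ)²].

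Take A = 40 µV, width 94 ms (σ = 0.0399 s) and 15 blinks per minute (λ = 0.25). The constant is 0.5 × 1600 × 6.283 × 0.001592 = 8.0. S at 4, 5, 6, 7 and 8 Hz is 2.93, 1.66, 0.83, 0.37 and 0.14. Simpson's rule gives (2.93 + 4 × 1.66 + 2 × 0.83 + 4 × 0.37 + 0.14)/3 ≈ 4.3 µV². Simulation with the stated filters and 2-second Welch windows gives 4.4. Simulated results at 40 µV and 15 per minute:

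| Blink width at half height | Added 4-8 Hz power | Share of 5-10 µV² true theta |
|---|---|---|
| 94 ms | 4.4 µV² | 44-88% |
| 141 ms | 1.6 µV² | 16-32% |
| 188 ms | 0.34 µV² | 3-7% |
| 250 ms | 0.03 µV² | 0.3-0.6% |

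The added power is proportional to λ, so 5 blinks per minute gives about one third of these values.

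A second simulation assumed Hann-shaped blinks of 15-60 µV lasting 0.2-0.4 s, on background theta of 3-5 µV RMS. Theta rose by 0% at 0 blinks per minute, 0.1-19% at 2, 0.1-89% at 10, and about 0-214% at 20. Its middle case (30 µV, 0.3 s, 10 per minute) gave 4-9%.

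**4. When does this reach an arm contrast?** Suppose blinks of 40 µV and 141 ms occur at 15 per minute in one arm and 5 in another. The spurious difference is 1.6 − 1.6/3 ≈ 1.07 µV², or 11-21% of 5-10 µV². With equal rates it is zero. A blink level that is stable within a person largely cancels when practice is compared with that person's rest. A task effect that is the same in Sessions 1 and 4 likewise cancels from the Session 1 to Session 4 change. What remains is eye behaviour that differs by task within a session, or that shifts between sessions differently by arm. The document has no data on either.

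**The case against.** The strongest reply is that this is a condensed article and silence is not a decision. The text never says eye activity will be left in, recording the EOG suggests a correction is intended, and the EEGLAB scripts are not shown. This stands against any claim that the investigators have chosen to leave blinks in. It does not remove the point, because the objection is to a stated sequence. Filter orders are given, artifact handling is written out for fNIRS, and the EEG recipe runs from PREP to theta without it.

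Other stronger readings are tempting and are not supported:

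- **Epoch length.** A reader might blame "First, epochs of 300 s will be created for each participant" for leaving no shorter unit to reject. Welch's method already averages over shorter windows within the epoch, so the length is not a fault.
- **Step order.** PREP follows the 40 Hz low-pass, which has already reduced 120 Hz by about 45 dB. That makes the later harmonic step largely redundant; it does no harm to 4-8 Hz power.
- **Bias between arms.** The control period is described only as matched in time. Nothing says participants are left without instructions or that they blink more or less. The two mindfulness arms share the first 10 of 15 practice minutes, and no reason for a blink difference between them is given.

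The size is also fairly disputed. The largest values need narrow or large, frequent blinks and low background theta.

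**Conclusion.** The concern holds in a conditional form. The pipeline as written contains no ocular correction or rejection, and its filters pass 4-8 Hz unchanged, so blinks can be counted as theta. Whether they are, and by how much, depends on eye state, blink rate, amplitude and width. Under the assumed values the effect runs from nothing (no blinks) through a few percent to a contribution as large as the signal or larger. No single figure can be defended from the document.

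A reader might infer that the theta contrast is already biased. The document does not support that. Bias in the arm contrasts, and its transfer to Aims 2 and 3, requires eye behaviour to differ between guided practice and the control period. Otherwise the blink energy is mainly added noise. The point deserves correction because the remedy is cheap and uses a channel already being recorded.

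**What to change.** Add to the EEG steps, before theta is computed:

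1. An ocular correction of the frontal channels based on the recorded vertical EOG. Regression is one method suited to a 10-channel montage. Apply it identically to rest, practice and control periods.
2. Exclusion of Welch windows with residual artifact, by a fixed rule applied blind to arm, with theta averaged over the windows kept.
3. A report of retained recording time and blink rate by arm and period, so that a reader can see whether eye behaviour differed.

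State the eye-state instruction in use, but do not change it now. Recruitment began on October 28, 2024, and a new instruction would put early and late participants under different recording conditions.

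The cost is a script change that also applies to data already collected. A few windows will be lost, and regression will remove a little true frontal signal.
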